## Method

### Trial design

This is a mixed methods study addressing objectives and testing hypotheses in a single blind *Randomised Controlled Trial* (RCT) (concealed allocation), adhering to CONSORT guidelines for transparent reporting [16], during which *Qualitative Evaluation* and FECH program *Process Evaluation* will also be undertaken. The study will also be supported by an expert reference group. The RCT will compare outcomes between the control condition (usual care) and the experimental condition (usual care plus family carer inclusion on the new FECH program). Approval has been received from the Sir Charles Gairdner Group Human Research Ethics Committee (HREC) (2014–133), the Department of Health WA HREC (2014/78), and from the Curtin University HREC (HR14/2015).

### Study setting and participants

The MAU is a 36-bed unit providing intensive assessment and treatment for patients with acute medical conditions, most of whom are over 70 years of age. MAUs are widely implemented in the UK, Australia and New Zealand in response to the need to increase patient through-put [17] and sustained health system pressures suggest that their use will continue to expand. Care is provided by physician-led multidisciplinary teams for up to 72 h, after which patients are discharged or transferred to inpatient units for ongoing management. A key component of the MAU model is that ongoing management for discharged patients is provided through prompt general practitioner follow-up [9].

Included participants will comprise dyads of older people (aged 70+) discharged home from the MAU during the recruitment period and their adult (aged 18+), English speaking, family carers (one per patient). The definition of a family carer is that used in a recent Australian study investigating the care of frail older people: “a family member or friend who provides unpaid personal care, support and assistance” [18]. Dyads already recruited into the study will be excluded from further recruitment upon any subsequent readmissions to the MAU.

### Experimental condition (inclusion in the FECH program)

Carer participants in the intervention group will receive standard care plus the FECH program implemented by the FECH nurse who will be appropriately skilled and trained. Currently there is no nurse involved in providing the FECH or any similar program to patients or carers.

Contacts will be made by telephone, after discharge (Fig. 1). The FECH Nurse will make initial contact with the family carer within one week of the discharge (Contact 1). This contact will include the FECH nurse introducing him/herself, explaining the intervention, and scheduling ‘Contact 2’. Contact 2 is likely to comprise a series of brief telephone interviews, if this is the arrangement that suits the family carer best, within the subsequent few days to (a) determine and respond to the extent to which the family carer understands the copy of the discharge letter to the general practitioner that has been provided to them; (b) administer the CSNAT [14] to the family carer, resulting in the carer’s self-identified and highest prioritised support needs; and (c) initiate responses to the three prioritised needs, helping ensure family carers’ linkage and engagement with appropriate existing resources. A few days after Contact 2 is finalised (within 14 days of the discharge), the FECH nurse will check to determine if access to support has been achieved as planned, advising as appropriate (Contact 3). This contact will include asking if the services have been sourced (eg, an appointment made) and/or if the service has been accessed. These three contact points will be coordinated with the three data collection time points (T1, T2, and T3) also shown in Fig. 1.

**Fig. 1 Fig1:**
[figure not shown]
Data collection and intervention points (experimental condition, family participants)

### Control condition (usual care)

Standard discharge ‘care’ includes the provision of a letter from the MAU’s physician to the patient’s general practitioner, with a copy provided to the patient. Medications are provided/organised by the MAU pharmacist. The MAU information booklet provides information about post-discharge support options and is intended to be taken home. Carers regarded as ‘at particular risk’ by the social work team receive social work assessment and links to services. Services put in place for patients may include a variety of care packages or programs. Information packs from Carers Australia are made available in the hospital rooms. Any one or more of these options considered by treating ward staff to be relevant to the patient and their carer will be provided as usual care.

### Carer outcome and data collection

#### Primary outcome variable

The primary outcome is preparedness for caregiving, to be measured with the Preparedness for Caregiving Scale (PCS) from the Family Care Inventory [19] (T1- T3). This measure is an 8-item scale, with five response options (0 = not at all prepared, 4 = very well prepared) and is designed for use with carers of older people receiving homecare or experiencing care transitions. Construct validity has been established in older people, and the measure has been shown to be reliable (Cronbach’s alpha coefficients: 0.88-0.93) [19]. Testing in patients with a life threatening illness confirmed satisfactory internal consistency reliability as well as unidimensionality [20].

#### Potentially confounding variables

Data on potentially confounding variables will be collected to help inform interpretation of results. Carer rated patient Symptom Assessment Scale scores [21] and carer rated scores evaluating dependence of the patient in ten activities (Barthel Activities of Daily Living Index) [22] will be collected (T1-T3). Robust psychometric properties have been documented for these tools. Carer resilience will be measured at T1 using the 10-item Connor-Davidson Resilience Scale [23].

#### Secondary outcome variables

Based upon recent findings using the CSNAT tool [24], caregiver strain will also be measured at each time point using the 25-item Family Appraisal of Caregiving Questionnaire [25]. Carers’ ratings of their own health will also be collected (T1-T3) using the SF12 Version 2, a tool exhibiting robust psychometric properties with older people [26]; this tool has been used in large scale surveys such as those with veterans in the United States [27].

#### Data collection

A Research Officer (RO1) will develop a schedule for collecting data from all participating family carers (both groups) by telephone, at the time of recruitment to the study. At baseline assessment (T1), RO1 will also collect demographic details of the patient and the carer from the carer, including the carer’s familial relationship with the patient, age and gender (carer and patient), highest education level, occupation, usual place of residence, country of birth, years in Australia, support provided for the patient, contact with the patient, length of time caring for the patient, education received to help in the caring role, location of care, whether currently living with patient (and if so, whether in patient’s or carer’s home), any care provided by others, and known current medical conditions (patient and carer). Brief, robust measures to minimise questionnaire burden will then be administered (each contact is estimated to last approximately 30 min). Questionnaire administration across the three assessments (T1, T2, and T3) is summarised in Table 1.

**Table 1 Tab1:** Planned questionnaire administration at each time point

Time 1	Time 2	Time 3
Demographic details		
Connor-Davidson Resilience Scale [23]		
Preparedness for Caregiving Scale [19]	Preparedness for Caregiving Scale [19]	Preparedness for Caregiving Scale [19]
Symptom Assessment Scale [21] (patient)	Symptom Assessment Scale [21] (patient)	Symptom Assessment Scale [21] (patient)
Barthel Activities of Daily Living Index [22] (patient)	Barthel Activities of Daily Living Index [22] (patient)	Barthel Activities of Daily Living Index [22] (patient)
SF12 [26]	SF12 [26]	SF12 [26]
Family Appraisal of Caregiving Questionnaire [25]	Family Appraisal of Caregiving Questionnaire [25]	Family Appraisal of Caregiving Questionnaire [25]

### Patient outcomes and data collection

Quantitative patient outcome data will address Western Australian health care system utilisation and will be obtained through linked administrative health data provided via the WA Data Linkage System (WADLS) [28]. These Data Linkage Unit (DLU) data will capture reason for service and mode of transport plus: date of service, symptom/presenting problem, and triage code (ED presentation); admission and separation dates, primary diagnosis code, co-diagnosis code, and diagnosis related group (hospitalisation data). In addition, to account for time at risk, and to capture deaths resulting from acute events during the study follow-up period, date and cause of death will be collected.

The data retrieved from data linkage will cover the time period from the date of the index separation of the patient whose carer is the first to be recruited to the study until 3 months after the index separation of the patient whose carer is the last to be recruited. Since recruitment is planned to last approximately 6 months, this time period will cover approximately 9 months.

### Sample size

The primary outcome is the total score on the Preparedness for Caregiving Scale [19]. An improvement of two points in the total score is regarded as clinically relevant, given that this would mean a change such as progressing to ‘very well prepared’ from ‘well prepared’ in 25 % of items. To detect a change of this magnitude with 80 % power (assuming that the standard deviation of the change in mean score is approximately 0.5, as in previous work) [19, 29] a sample size of 63 per group will be required. Based upon previous studies by the research team, attrition of approximately 30 % is expected so a sample of 180 carers in total will be recruited.

### Recruitment and randomisation

Figure 2 shows the proposed study flow. There were more than eight MAU discharges of patients aged 70+ each day in 2013, approximately half returning home (estimated 120 per month). Therefore, recruitment of 180 participants is considered achievable within the 6 month recruitment period (30 per month).

**Fig. 2 Fig2:**
[figure not shown]
Modified consort diagram to illustrate trial study flow and participant numbers

Although the primary study outcome relates to carers of patients discharged from the MAU, other outcomes relate to the former patients themselves so carer/patient dyads will be recruited. Whenever a patient aged 70 years or older is admitted to the MAU during the recruitment period, family carers - and, when appropriate, patients - will be provided with information about the project and asked to provide written consent to participate in the study by RO1. However, many patients are likely to be too unwell to be approached with information about the study during their hospitalisation and are likely to experience ongoing poor health that may also fluctuate [9]. Others will lack (cognitive) capacity to consider consenting. In these instances, data about patients’ use of health care services will be sought via a waiver of consent. An opt out form will be provided for such patients in case there is a later opportunity – if and when the patient’s health has improved – for them to withhold consent for inclusion of their data in the study, should this be their wish.

To facilitate the assignment to group (control or intervention) of participants, a list of treatment allocations will be prepared before the study commences; it will contain a study number (whole number, starting from one), and a code to indicate the group (intervention or control). The list of codes will be obtained using a sequence of computer-generated random numbers, and organised so that recruitment to the two study arms occurs at an approximately equal rate (using a permuted random block strategy). Allocation of participants to their treatment group will occur as follows: as each new dyad is recruited to the study, the next study number will be allocated to them (next in sequence on the list), and the treatment allocation for that study number will be read from the list.

### Qualitative feedback from patients and family carers

An ‘exit’ telephone interview will be conducted with an estimated 30 carers in the intervention group and, when possible, the older people receiving care from them (estimated 20). These participants will be purposively sampled on the basis of questionnaire data to cover a wide variety of carer profiles (eg, carer sex, age [older versus younger carers], duration of caregiving [new carers versus those who are more experienced], relationship to patient [husbands, wives, sons, daughters, others], and location of care). The sample will be extended if issues need further exploration and until data saturation is reached.

Interviews will occur within two weeks following administration of the final measures, to: investigate how the FECH model affected the participants, assess the support provided, identify factors influencing feasibility/usefulness, and assess how the FECH model could be improved. Written informed consent for participation will be obtained separately for this step and will involve mailing the information sheet and consent forms (for the carer and for the patient); then following up with a phone call during which questions can be answered, before requesting the return of the completed consent form in a prepaid study envelope. It is anticipated that the interviews will take approximately 30 min. A second telephone call will be offered if the interview takes longer than 30 min and the carer wishes to provide further relevant information.

### Qualitative feedback from the hospital staff

A focus group interview will be convened with the MAU staff as soon as carer recruitment for the trial has been completed. The staff working on the unit during the trial will be invited to take part and will be asked to comment on any impact from the FECH program on the Unit and to suggest: program refinements that would minimise negative outcomes and maximise those that are positive, how the program could be integrated into practice, and how its sustainability could be addressed. The staff members will be invited to take part by mail, and will also be sent an information sheet and consent form.

### Process evaluation

Evaluation of FECH program processes will involve the FECH nurse documenting, during the trial: (a) adherence to, or deviation from, planned FECH processes; (b) information provided to carers and the resources to which they were referred; (c) the extent to which carers engaged with resources; (d) the contextual factors that were barriers to, or facilitators of, resource and service access and engagement; and (e) costs issues – primarily time taken to implement processes. This documentation will be achieved using an electronic database developed at the same time as the process manual and completed by the FECH nurse as the process is implemented.

### Blinding

Group assignment will be concealed from RO1. When RO1 conducts the T1-T3 data collection telephone questionnaire administration, he or she will commence the conversation with a request to the participant (the carer) not to mention any phone calls from other study personnel. This reminder will not always be sufficient to prevent disclosure, and instances when it occurs will be documented to inform study reports. In a previous study, quantification of any ‘unblinding’ involved asking the hospital staff to identify to which group they thought patient participants had been assigned [30]. In this study, a similar question will be asked of the research staff collecting outcome data. The person conducting the qualitative interviews will be a Research Officer employed for this purpose alone (RO2), so that blinding to group allocation will be maintained for RO1. Investigator blinding will also be maintained by allocating responsibility for this (qualitative) component of the study to one of the research team, an experienced qualitative researcher who will not be involved in quantitative data collection or analyses.

### Statistical analysis

Data analyses will be performed using the IBM SPSS statistical software package [31]. A p-value of <0.05 will be taken to indicate a statistically significant result in all tests.

#### Baseline data

Standard descriptive statistics (means, standard deviations, medians for continuous variables and frequencies and percentages for variables measured on a categorical scale) will be used to summarise the characteristics of participants in the study (primarily demographic data, but also including some data relating to the care recipient to describe the caregiving situation). Chi-square tests and t-tests will be used to compare the treatment groups (intervention versus control) on the basis of these variables. It is anticipated that there will be no significant differences between groups in terms of demographic characteristic or potentially confounding variables, which will confirm that the randomisation process has allocated participants evenly to each arm of the study.

#### Carer outcome

Outcome analysis will be conducted using an Intention to Treat approach. The change in the total Preparedness for Caregiving Scale [19] score between T1 and T3 will be calculated for each carer. An initial *t*-test will compare changes between treatment groups. If changes in scores are not normally distributed, a non-parametric method will be used instead (Wilcoxon 2-sample test). In the (unlikely) event that groups differ on the basis of baseline variables, a regression model will be used instead of the *t*-test, so that these potentially confounding variables can be taken into account. A random effects regression model will be used to examine changes in the Preparedness for Caregiving Scale score over all three data collection periods (instead of just baseline/end of study). This model will be used so that correlations between measurements made on the same participants can be taken into account. Results of the model will help show whether changes in scores happen soon after recruitment, or later. The model can be extended to adjust for other potentially confounding variables.

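### The Intention to Treat label does not fit the first-line change-score test, which drops about 54 of 180 carers, and the plan does not say whether that test or the all-data model decides H1

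*Protocol article*

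**What the plan says.** The Carer outcome section opens with "Outcome analysis will be conducted using an Intention to Treat approach". It then derives a change in the Preparedness for Caregiving Scale total: the "score between T1 and T3 will be calculated for each carer". A t-test, described as initial, follows ("test will compare changes between treatment groups"). A Wilcoxon test replaces it if changes are not normal, and a regression replaces it if the arms differ at baseline.

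The same section adds: "A random effects regression model will be used to examine changes in the Preparedness for Caregiving Scale score over all three data collection periods". This model is meant to handle correlation within carers, to help show when change occurs, and to allow adjustment for confounders.

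Under Sample size, "An improvement of two points in the total score is regarded as clinically relevant", and 63 carers per group are required, "assuming that the standard deviation of the change in mean score is approximately 0.5, as in previous work". Attrition of about 30% "is expected so a sample of 180 carers in total will be recruited". The Abstract gives the number who must complete as 126. Under Statistical analysis, "A p-value of <0.05 will be taken to indicate a statistically significant result in all tests".

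**The concern.** A carer with no T3 score has no T1 to T3 change. The t-test therefore compares completers only, and the T1 and T2 scores of everyone else go unused. Both fallbacks have the same limit, because each replaces the t-test on that same change. The plan expects this for three carers in ten.

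The plan also contains an analysis that would use the partial records. The two analyses address one outcome at one significance threshold, and no rule says which counts if they disagree. The t-test comes first, is the only one with named fallbacks, and is the one the sample size matches. A reader could well take it as decisive.

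Only one arm receives nurse calls, and carers know whether they receive them, so reasons for leaving could differ by arm. If they do, a completer comparison can be biased in either direction.

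**Working it through.** **Reproducing the plan's figures.** Two points on an 8-item total is 2/8 = 0.25 on the item-mean scale. The stated SD of 0.5 fits that scale and equals 0.5 × 8 = 4 points on the total. With a two-sided 5% test (sidedness is not stated) and 80% power:

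- n per group = 2 × (1.960 + 0.842)² × (0.5/0.25)² = 2 × 7.85 × 4 = 62.8, so 63. This matches.
- Completers: 2 × 63 = 126. Recruited: 126/(1 − 0.30) = 180. Both match.
- Carers outside the t-test at that attrition: 180 × 0.30 = 54.

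The sample size is therefore that of the change-score t-test on completers.

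**Size of the possible bias.** The documents give no dropout pattern, so the following are assumptions: 90 carers per arm; no true effect; score SD 4; correlations 0.60 (T1, T2), 0.50 (T1, T3) and 0.65 (T2, T3); about 30% lost, all after T2. The SD of change is then √(2 × 16 × (1 − 0.50)) = 4, as in the plan. Dropout is logistic in the T1 score or in the T1 to T2 change, with slopes per SD set separately for each arm.

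| Dropout slopes (arm, arm) | Bias of change-score t-test | Its type I error |
|---|---|---|
| Equal | none | about 5% |
| 0.5, 0.25 | about 0.13 to 0.18 points | about 6% |
| 1, 0 or 0.5, −0.5 | about 0.5 to 0.7 points | about 11 to 18% |

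The all-data likelihood estimate is biased by at most about 0.02 points.

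**Check by formula.** The SE of the t-test is 4 × √(2/63) = 0.71. A bias of 0.5 gives 0.5/0.71 = 0.70 and a rejection rate of Φ(−1.26) + Φ(−2.66) = 11%. A bias of 0.7 gives 0.7/0.71 = 0.98 and Φ(−0.98) + Φ(−2.94) = 17%.

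A separate simulation used all correlations 0.75, SD of change 4, random 30% loss in controls, and loss depending on early change in the intervention arm. The t-test had a bias of 0.75 points and a type I error of 18%. The random effects model had 0.03 points and 5%.

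**Separating baseline adjustment from partial records.**

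- If dropout depends on T1, completers adjusted for T1 are already unbiased (at most 0.02 points; type I error 4.6 to 5.5%).
- If dropout depends on early change with markedly different slopes, adjusted completers remain biased by 0.4 to 0.8 points, the upper end for strongly opposed slopes. Here the partial records are needed.
- Under random loss the SE is about 0.72 for the t-test. Adjusting completers for T1 brings it to 4 × √(1 − 0.50²) × √(2/63) = 0.62, and using all data to about 0.60. Most of the gain comes from baseline adjustment.

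**The case against.** A reader might infer that the trial's primary analysis is a completer analysis and that the Intention to Treat claim is false. The article does not support that. It calls the t-test initial, not primary. The Abstract names regression for group differences over time and states Intention to Treat directly afterwards, which can be read as attaching the principle to the longitudinal model. That model has more than a descriptive role, since it handles within-carer correlation and can be adjusted. Intention to Treat is also used to mean analysis by allocated group, and nothing contradicts that sense. A rule for missing scores may sit in the full protocol or analysis plan, so its absence here is no fault.

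A reader might also infer a seriously inflated type I error. The documents do not say that dropout depends on scores or differs by arm. The larger biases need clearly different slopes, and placing all loss after T2 favours the all-data model.

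These arguments lower the severity. They do not settle which analysis decides H1, or change the fact that the first-listed test and both its fallbacks, as written, need both scores.

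**Conclusion.** The point holds in limited form. The stated principle does not fit the first-line test if it is meant to cover all randomised carers: that test uses about 126 of 180. The analysis that would fit better is already planned but is not named as deciding.

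The consequence ranges from lost precision only, through about 0.1 to 0.2 points, to about 0.5 to 0.7 points against a relevant difference of 2. Where a trial falls in that range depends on how dropout differs between arms, which cannot be known in advance. The figures rest on the assumed correlations, the SD of 4 and loss after T2. The model's protection requires that dropout depend only on observed scores. Severity: should-fix, a cheap improvement.

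**What to change.** State one deciding analysis for H1: the random effects model over T1, T2 and T3, with all randomised carers who have at least one score, by allocated group. Use categorical time, a group-by-time interaction, T1 preparedness as a covariate or a common baseline mean, and the group difference at T3 as the estimate. Keep the T1 to T3 change-score t-test, with its fallbacks, as a sensitivity analysis.

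The cost is wording. Visits, data and sample size stay as they are. The random effects model is already planned, but the time coding, T1 adjustment and T3 contrast are additions to the present text. The primary estimate becomes slightly more complex than a difference in mean change. Carers lost before T1 contribute to neither analysis, so their number should be reported by arm. T1 adjustment also presumes that T1 is taken before the nurse's first call; the figure showing that order is not available here, so it should be confirmed.

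### The primary carer analysis is chosen by baseline tests and a normality check instead of being fixed in advance, and the baseline trigger called unlikely has about even odds or better

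*Protocol article*

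**What the plan says.** The Carer outcome section of the protocol article calculates each carer's T1 to T3 change in total PCS and compares the arms with a t-test. Two rules can displace that test. The first concerns distribution: "If changes in scores are not normally distributed, a non-parametric method will be used instead (Wilcoxon 2-sample test"). The second concerns baseline balance: "In the (unlikely) event that groups differ on the basis of baseline variables, a regression model will be used instead of the" t-test. A random effects model over all three time points is also planned, without saying whether it is primary or supportive.

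The Baseline data section compares the arms by chi-square and t-tests. It expects no significant differences in demographic or potentially confounding variables, "which will confirm that the randomisation process has allocated participants evenly to each arm of the study". The Statistical analysis section sets the threshold: "A p-value of <0.05 will be taken to indicate a statistically significant result in all tests".

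The article gives no criterion for non-normality, no order of precedence if both rules fire, and no list of covariates for the replacement regression.

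**The concern.** Three things look wrong.

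- **The primary analysis is not fixed.** The method, the covariates and even the quantity tested (a difference in means or a shift in ranks) are settled only after the data are seen. The sample size calculation belongs to just one of the three possible analyses.
- **The reasoning behind the trigger does not hold.** Allocation is by a computer-generated permuted-block list, so differences between the arms in characteristics that allocation cannot affect are chance. A non-significant test does not verify the process. A significant one does not show that the variable predicts preparedness, which is the only good reason to adjust for it.
- **The default is not the most precise use of the data.** A T1 PCS score is collected from every carer, yet adjustment for it is never fixed in advance.

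At stake is the credibility of the single primary result. A reader of the trial report could not tell whether the analysis shown was the planned one or the most favourable of several permitted ones.

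**Working it through.** **1. Reproduce the sample size.** Inputs from the Sample size section: a target of 2 points on the total score ("An improvement of two points in the total score is regarded as clinically relevant"), 80% power, and an SD described thus: "assuming that the standard deviation of the change in mean score is approximately 0.5". Alpha is 0.05, taken as two-sided. The PCS has 8 items, so an SD of 0.5 per item is 8 × 0.5 = 4 on the total score.

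n per arm = 2 × (1.960 + 0.842)² × 4² / 2² = 62.8, so 63. This matches the protocol, and 126 / 0.70 = 180 matches the recruitment target. An SD of 0.5 on the total score itself would give 1 per arm, so 4 is the working value. Power at 63 per arm is 80.1% by the normal approximation and 79.5% by the exact t-test.

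**2. How likely is the baseline trigger?** The Data collection section lists about 19 demographic and caregiving items (age, gender and medical conditions counted once each for carer and patient). The section on potentially confounding variables adds three scales: symptoms, Barthel and resilience. That makes about 22. The article does not state the number of tests, so this count is an assumption, as is reading a baseline difference as p < 0.05.

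Under proper randomisation and independence, P(at least one p < 0.05) = 1 − 0.95^k:

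| k | Probability |
|---|---|
| 10 | 40% |
| 13 | 49% |
| 14 | 51% |
| 19 | 62% |
| 22 | 68% |

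Many of the items are related (country of birth and years in Australia, for example). Monte Carlo with a common correlation between the test statistics of 0.2 and 0.4 gives 59% and 48% for 20 variables, and 64% and 52% for 23.

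**3. What does switching do to error rates?** Simulation: 6,000 trials per setting; 63 per arm; change SD 4; 20 independent baseline variables, four of them prognostic; T1–T3 correlation 0.5 or 0.7; Shapiro–Wilk p < 0.05 as an assumed non-normality trigger.

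- The baseline trigger fired in 65% of trials.
- Type I error with the rule followed mechanically was 0.040 to 0.048. Picking the smallest of the available p-values gave about 0.067.
- Power for a 2-point effect was 0.78 to 0.79 for the switching rule, about 0.79 to 0.80 for the t-test alone, and 0.89 (correlation 0.5) or 0.85 (0.7) for a pre-specified ANCOVA on T1 PCS.

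**4. What does fixed adjustment for T1 gain?** With equal variance σ² at T1 and T3 and correlation ρ, the change score has variance 2σ²(1 − ρ) and the ANCOVA residual has variance σ²(1 − ρ²). The ratio is (1 + ρ)/2. Holding the change SD at 4, the residual SD is 4 × √((1 + ρ)/2). The article does not give ρ, so a range is shown (normal approximation):

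| ρ (assumed) | Variance ratio | Residual SD | Power at 63 per arm | n per arm for 80% |
|---|---|---|---|---|
| Change score | 1.00 | 4.00 | 80% | 63 |
| 0.5 | 0.75 | 3.46 | 90% | 48 |
| 0.7 | 0.85 | 3.69 | 86% | 54 |
| 0.8 | 0.90 | 3.79 | 84% | 57 |

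**The case against.** The strongest defence is that little demonstrable harm follows. Type I error is not inflated when the rule is followed as written, and power falls by only a point or so against the t-test alone. The change-score t-test is unbiased over randomisations and agrees with a sample size built on the SD of change. The random effects model is planned unconditionally. All of this stands, and it limits the point to a recommended improvement. It does not answer the lack of a single named primary analysis, because the role of the random effects model is unstated.

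Several stronger readings are tempting and should be resisted:

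- **That the 5% level is lost.** The 0.067 figure needs deliberate selection among p-values, which the article does not propose. What the wording leaves is room for such selection.
- **That the T1 score is discarded.** A change score uses T1, though inefficiently.
- **That a significant baseline test is nearly certain.** This would require counting the T1 outcome scales (PCS, SF12, caregiver strain), which the Baseline data section does not list for testing, and treating related items as independent.
- **That T2 and T3 symptom or Barthel scores will be adjusted for.** They are collected at all three times ("Barthel Activities of Daily Living Index) [22] will be collected (T1-T3"), and the random effects model may be extended to further confounders. But the article never says that post-randomisation values will enter it, and the replacement regression refers to baseline variables.

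One objection bears on the remedy. Dyads are allocated as they are recruited, at discharge. T1 falls within 4 days of discharge and Contact 1 within one week. T1 can therefore follow allocation, and the text sets no order between T1 and Contact 1 (Figure 1, not seen here, may show one). Adjustment for T1 PCS is safe only if T1 comes first; the planned change score needs the same condition.

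**Conclusion.** The point holds as a should-fix item. The article lets observed data choose among three primary analyses, gives a mistaken reason for the baseline tests, and calls unlikely a trigger that would fire in roughly half to two thirds of properly randomised trials. That range assumes about 19 to 22 tests at 0.05 and correlation from none to 0.4. The chance drops below one half only with 13 or fewer independent tests or with stronger correlation.

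The cost is an undefined primary analysis, scope for selective choice and avoidable imprecision, not a loss of validity. Fixed adjustment for T1 PCS is worth about 4 to 10 percentage points of power at 63 per arm, for an assumed ρ of 0.8 down to 0.5, given equal T1 and T3 variances and a change SD of 4.

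A separate analysis plan might name one analysis. The point nevertheless rests on what the article states, so that wording would still need correcting.

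**What to change.** - Delete both switching rules.
- Name one primary analysis in advance: T3 PCS compared between arms, always adjusted for T1 PCS, either by ANCOVA or by the already planned random effects model with T1 treated as baseline. State which is primary.
- Take any further covariates from a short pre-named list of T1 values chosen because they are expected to predict preparedness. Limiting the list to T1 values also settles the question of later symptom and Barthel scores.
- Report baseline characteristics descriptively without p-values, and remove the statement that the tests verify randomisation.
- Keep the Wilcoxon test as a sensitivity analysis only.
- State that T1 is collected before Contact 1, so that it is a true baseline.

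The analysis changes are wording only, with no new data, participants or visits, and should be made before outcome data are analysed by arm. The last item asks only that the order of two already planned telephone calls be stated and kept.
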